#### Identification of local champions and clinical experts

Champions at the three intervention facilities will participate as clinical leads at the three intervention sites. Formative evaluations identified that local champions, such as local infectious diseases specialists and antimicrobial stewardship and infection control experts, are major drivers of sustained practice improvement, consistent with published data [28, 29]. These champions are the ideal *internal facilitators* for promoting practice improvement for several reasons. First, reducing infections and improving antimicrobial use are central aspects of their clinical and administrative duties [7, 30, 31]. These champions have protected clinical and administrative time dedicated to improving antimicrobial use [32] and are passionate about promoting the safe and effective use of antimicrobials [33]. Second, as part of their clinical and administrative rules, local antimicrobial stewardship content experts are empowered to revise local protocols and CIED infection prevention guidelines. However, they do not have the necessary technological support to measure rates of CIED infection or compliance with guideline-concordant practice and thus have limited resources to promote change; the automated audit and feedback system included as part of the implementation intervention addresses this critical need.

#### Education

Education of both providers and patients will be included. Educational sessions for providers will provide information about (a) clinical guidelines, (b) harms associated with guideline non-compliance, and (c) the audit and feedback reports. Educational sessions will be scheduled to coincide with standing conferences, such as grand rounds, infection prevention committee, and/or morbidity and mortality, to enhance attendance and knowledge about the program and its goals. Patient education materials will be developed and distributed; these will be developed by a graphic medicine specialist and will include information about the risks and benefits of peri-procedural antimicrobial use and things that a patient can do to prevent and identify infections.

#### Blended facilitation

Facilitation is a critical aspect of the iPARIHS framework and will be addressed internally and externally (i.e., blended). The preliminary results highlight the degree to which current practice is determined by normative factors; thus, providing feedback about the overall shift in clinical practice and resulting outcomes may promote de-adoption of guideline-discordant practice by limiting provider concerns about “being an outlier” and medical malpractice concerns associated with not adhering to the locally entrenched, but not evidence-based, standard of care. The implementation strategy external facilitation will be achieved through in-person or virtual educational sessions, centralized data collection and verification through reports, and site check-ins (either virtually or in-person, depending upon what is feasible given the pandemic) that will encourage participation and allow progress to be reviewed. Internal facilitation will be achieved by local champions, who will provide educational sessions, present the data to providers, encourage uptake of evidence-based practices, and collaborate with electrophysiology team members to develop local policies and procedures.

##### Study setting

Three large volume, VA medical centers were selected based on (1) high volume of procedures (e.g., >100 procedures per year), (2) high rates of inappropriate antimicrobial use (>50%), and (3) operating characteristics of all elements of the semi-automated surveillance tools during the development and validation of the electronic monitoring tool that will be used for the audit-and-feedback reports [13, 34].

##### Study design

A stepped-wedge implementation/effectiveness trial will be conducted at three VA medical centers.

##### Study timeline

An overview of the stepped-wedge process is presented in Table 2. The implementation intervention will be rolled out at different sites at different times and will occur in several phases.

#### Phases of the stepped/wedge design

##### Phase I: educational sessions and feedback from sites about audit and feedback reports

Educational seminars and/or webinars developed by the coordinating site and provided to clinical infectious diseases champions at the intervention sites will be presented to electrophysiology team members. Educational sessions will focus on benefits of pre-procedural antimicrobial prophylaxis, harms of post-procedural antimicrobial prophylaxis, and strategies for reducing infection. The semi-automated audit and feedback surveillance system with site-specific data available on a secure dashboard will also be introduced.

##### Phase II: wash-in, initiation of locally adapted reports

Prior to providing the audit and feedback reports, the local champions will be asked to provide input about the accuracy of the semi-automated algorithm for detecting true adverse events and about usability and feasibility. Based on feedback, the surveillance tools and reports will be locally adapted to each of the participating study sites. After local adaptation, sites will be provided with monthly surveillance reports, which will be manually validated by the primary study site. Champions at each site will be contacted and informed that the reports are available and ready for review via a protected and shared server with capabilities to monitor frequency of report access (measure of site fidelity to the intervention).

##### Phase III: reports provided

Monthly reports developed on previously published semi-automated electronic data extraction algorithms [34] that include concordance with guideline-based antimicrobial use practices at the facility and benchmarked to practices from the entire VA healthcare system, cardiac device infections and rate, and non-cardiac adverse events (AKI, *C. difficile* infections) will be provided to the local champions via the secured shared site. Thus, the information will be available for monthly conferences. Sites that do not access the reports for a 2-month period will be contacted by email to encourage report access and use (i.e., external facilitation). If email is not effective, sites will be contacted via phone and local infectious diseases champions will be asked about the lapse, support will be offered, and use encouraged. Intermittent site visits (either virtual given the pandemic or in-person) will also be used to encourage participation.

##### Phase IV: data analysis

During the last year of the project, qualitative and quantitative summative data will be analyzed. Quantitative data will be analyzed to measure *adoption* (through change in proportion of cases with guideline-concordant practice) and *fidelity* (measurement of report access). Quantitative data about clinical endpoints (*C. difficile* infections, AKI) will be extracted from electronic health records (EHRs) and analyzed. The wash-in period will be excluded. Qualitative will be collected through semi-structured interviews (in-person or virtually) with key stakeholders.

#### Trial outcomes and assessments of effectiveness

This study will collect quantitative and qualitative data. The primary outcomes are implementation outcomes, with clinical outcomes secondary.

### Implementation outcomes

#### Primary outcome (implementation outcome, adoption of evidence-based practice)

The primary outcome measure of the hybrid type III trial is the change in the proportion of cases with guideline-concordant antimicrobial discontinuation within 24 h after skin closure, which is the guideline-recommended and evidence-based practice. Antimicrobial use patterns pre- and post-implementation will be measured using the previously described automated algorithm for measuring peri-operative antimicrobial prophylaxis, which has >**97%** accuracy at the three participating sites. The adoption and maintenance of guideline-concordant pre-procedure prophylaxis and de-adoption of guideline-discordant post-procedure prophylaxis will be measured quantitatively as a change in proportion of procedures with guideline-concordant practice using longitudinal data from three VA study sites. Assessments of audit and feedback report access and use by the study sites will be performed to ensure that the reports are being accessed and used as a measure of fidelity. Specifically, implementation fidelity will be measured quantitatively using access to reports and will be measured by calculating the number of months reports were available/number of months reports were accessed; sites will then be assigned a fidelity rank score (high, moderate, low) based on report access.

Additional information about the effectiveness of the multi-faceted implementation strategy for other implementation outcomes (e.g., feasibility, fidelity, acceptability) will be collected during qualitative interviews of key stakeholders at each of the three sites.

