### Data analysis

#### Analysis of quantitative data elements

The primary outcome measure is the *adoption* of guideline-based pre-procedure prophylaxis and *de-adoption* of guideline-discordant post-procedure prophylaxis, defined as a change in the proportion of procedures with guideline-concordant antimicrobial use practices. This will be assessed by using an interrupted time-series analysis at the three study sites with comparison of proportions, accounting for facility and random fixed-effects. A regression model adjusted for patient and facility characteristics will then be used to estimate the impact of fidelity of accessing reports on adoption of guideline-based practices.

The quantitative effectiveness (primary outcome) of the implementation strategy will be measured through the change in the adoption of evidence-based antimicrobial use at the three sites. This will be calculated as the change in proportion of cases *without* post-procedural antimicrobials lasting for >24 h after skin closure, as measured by the automated algorithm. The analysis will use a generalized linear mixed model to estimate the probability of pre-and post-implementation antimicrobial use, accounting for facility-level correlation as a random effect. We will also explore the influence of calendar time in the Stepped-Wedge Design using models described by Nickless et al. [35].

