### Power calculations

#### Adoption of evidence-based practices (primary outcome)

Using the power estimation procedure of Hussey and Hughes [36], we will need to evaluate 135 cases from each site, inclusive of before and after the surveillance system is active, and setting alpha = 0.05, we will have 80% power to detect a difference in proportion greater than or equal to 0.15. In other words, if the rate of guideline discordant antimicrobial use in an individual facility changed from 50 out of 100 procedures to 35 out of 100 at each site after introduction of our audit and feedback system, we could detect a significant change in proportion. We assumed a coefficient of variation equal to 0.2 for this estimate. The three facilities perform >100 CIED procedures per year and all have rates of guideline discordant antimicrobial use following > 50% of procedures.

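### The fidelity ratio is written upside down, and a fidelity regression built on three site-level values is either not identifiable or inseparable from other site differences

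*Protocol article*

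**What the plan says.** In the protocol article, the section on the primary outcome states that "implementation fidelity will be measured quantitatively using access to reports". It gives the calculation as "number of months reports were available/number of months reports were accessed", and continues that "sites will then be assigned a fidelity rank score (high, moderate, low) based on report access". This is the only quantitative definition of fidelity in the article. The section on phase IV also names fidelity as a quantity to be analysed.

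The section Analysis of quantitative data elements adds a follow-on model: "A regression model adjusted for patient and facility characteristics will then be used to estimate the impact of fidelity of accessing reports on adoption". It does not say whether fidelity enters as the three-level rank, as a numeric score or month by month. It also does not say which facility characteristics are meant.

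The design has three sites: "A stepped-wedge implementation/effectiveness trial will be conducted at three VA medical centers".

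**The concern.** There are two problems, one of definition and one of information.

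First, the ratio runs against the concept it is meant to measure. A site that opens every report gets the lowest possible value, and a site that opens none gets no value. Anyone programming the formula as printed would order the sites backwards, or obtain a fidelity coefficient with the wrong sign. Lapses in access are foreseen, since the section on phase III provides that "Sites that do not access the reports for a 2-month period will be contacted by email to encourage report access and use".

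Second, fidelity is scored once per site and there are three sites. Such a score competes with every other site-level variable for two between-site degrees of freedom. The planned adjustment for facility characteristics, in the plural, can use these up. At stake is the stated estimate of how fidelity affects adoption: it may not exist, or it may only restate how the three sites differ.

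**Working it through.** **Inputs.** The ratio, the three-level rank and the planned regression are quoted above, and the number of sites is three. Reports are monthly: "After local adaptation, sites will be provided with monthly surveillance reports". Report periods come from Table 2. The power section says "we will need to evaluate 135 cases from each site, inclusive of before and after the surveillance system is active"; this serves only to size the matrices (3 × 135 = 405 rows). The article gives no numeric fidelity value or coefficient, so there is no stated figure to reproduce. Site-level values in the matrices were invented for illustration. The ranks do not depend on them, barring accidental collinearity.

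**Step 1: the ratio.** Let A be months available and U months accessed, with U ≤ A. As written, the score is A/U, the reciprocal of the access share U/A. It is therefore at least 1 and falls as access rises.

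| A | U | A/U (as written) | U/A (inverted) |
|---|---|---|---|
| 12 | 12 | 1 | 1 |
| 12 | 6 | 2 | 0.50 |
| 12 | 3 | 4 | 0.25 |
| 12 | 1 | 12 | 0.08 |
| 12 | 0 | undefined | 0 |
| 18 | 9 | 2 | 0.50 |
| 18 | 1 | 18 | 0.06 |

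**Step 2: what three sites can support.** Columns that are constant within site span at most three dimensions: an intercept plus two site-level parameters. With k site-level parameters, 3 − 1 − k between-site degrees of freedom remain. Each model below also has an intercept and one patient covariate.

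| Coding | Columns | Rank | Reading |
|---|---|---|---|
| Three distinct ranks | 4 | 4 | saturated between sites |
| Three distinct ranks + 1 facility characteristic | 5 | 4 | not identifiable |
| Numeric score | 3 | 3 | 1 site df left |
| Numeric score + 1 facility characteristic | 4 | 4 | saturated between sites |
| Numeric score + 2 facility characteristics | 5 | 4 | not identifiable |
| Two sites sharing a rank + 1 facility characteristic | 4 | 4 | saturated between sites |
| Numeric score + facility fixed effects | 5 | 4 | fidelity aliased |
| Facility effects, period, period × numeric score | 6 | 6 | estimable, from three site changes |
| Facility effects, period, period × three ranks | 7 | 7 | saturated |
| The same + period × 1 facility characteristic | 8 | 7 | not identifiable |
| Facility effects, period, monthly access | 6 | 6 | estimable within site |

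More procedures per site add rows but do not raise these ranks.

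**Step 3: data for a month-level model.** Counting the report columns of Table 2 after wash-in, and taking the column printed 30–46 to end at month 36:

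- Site 1: 3 + 3 + 6 + 6 = 18
- Site 2: 3 + 6 + 6 = 15
- Site 3: 6 + 6 = 12
- Total: 18 + 15 + 12 = 45 site-months

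If the column does end at month 46, the total is 28 + 25 + 22 = 75.

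**The case against.** The strongest reply has four parts.

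- **Direction.** The sentence with the ratio goes on to base the rank on report access, so a careful reader would rank the site with most access as high. This stands. One might infer that the reported ranking will be reversed, but the article supports that only if the fraction is applied mechanically. The formula still contradicts its own purpose and fails at zero access.
- **Identifiability.** One might also infer that the regression cannot be estimated at all, or that fidelity is fully aliased with facility. The article does not support that. It names no facility dummies for this model and does not fix the coding of fidelity, and for the primary mixed model it treats facility as a random effect. Several codings in the table have full rank. What survives is narrower: fidelity is defined only per site, the adjustment names facility characteristics in the plural, and the codings closest to that text are saturated or rank-deficient. The full-rank codings based on a site score still compare only three sites.
- **Left to the analysis plan.** Covariate coding commonly is. But the article itself fixes the site-level score and the kind of adjustment, and the two fit badly together.
- **Causal caution.** The limitations section already restricts causal attribution because the design is not randomised. It does not address fidelity.

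**Conclusion.** The point holds in a limited form. The ratio is wrong as written: its minimum is 1 at perfect access, it grows as access falls, and it has no value at zero access. The intended direction can be recovered from the same sentence.

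The fidelity regression rests on at most three site-level values. It is not identifiable with three distinct ranks plus a facility characteristic, or with a numeric score plus two facility characteristics. In simpler site-level codings it can be fitted, but the coefficient cannot be separated from other differences between sites. This assumes that fidelity enters as the per-site score, the only form the article defines.

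The regression follows on from the primary comparison. The primary outcome, its mixed model and its power calculation are untouched. The correction should be made, but it does not bear on the main result.

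**What to change.** 1. Define fidelity as months accessed divided by months available, running from 0 (never) to 1 (every month).
2. Report the three-site fidelity ranking, and its relation to adoption, descriptively.
3. If a regression is kept, use monthly report access as a time-varying exposure with facility effects, calendar time and patient covariates, and without added site-level characteristics. Label it exploratory. State the number of site-months (about 45 on the reading of Table 2 above) and clarify where that column ends.
4. State two limits of that model. Outreach after two months without access affects later access, so the two are entangled. And a site that opens every report contributes no within-site contrast between accessed and unaccessed months.

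The first change is one line. The month-level model should need no new data, provided that the shared server's capability to monitor access is used to keep a record by month; this should be confirmed. The cost is less reach for the fidelity analysis, which would no longer claim an adjusted site-level effect. The primary analysis stays as it is.

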### Clinical outcomes

#### Non-cardiac adverse events

##### Laboratory-defined AKI and *C. difficile*

A *C. difficile* infection is defined as a positive stool test from the initial date of antimicrobial exposure to within 90 days following the last day of antimicrobial prophylaxis. AKI is defined as occurring from the initial date of antimicrobial exposure to within 7 days of the last dose of antimicrobial prophylaxis and is based on AKIN-Network definitions. AKI severity will be reported (stages I, II, or III).

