	Observable results	All variables that will be included in the tool are extractable from the rich VA EHR. Variables that will be extracted electronically include number of procedures with and without guideline-concordant pre-procedure prophylaxis and guideline-discordant post-procedure prophylaxis and facility rank, 90-day CIED infection rate and facility rank, 7-day incidence of acute kidney injury, 90-day incidence of *C. difficile* infection. Manual review will be used to augment the electronic data pull, and qualitative analysis will be used to enrich the quantitative data.
Recipients	Motivation, values, and beliefs	Clinicians express a desire to ensure their patients have the best outcomes. This implementation strategy highlights the safety of stopping antimicrobials- and that stopping antimicrobials improves the overall health of their patients by (1) not increasing risk of infection, and (2) decreasing the incidence of patient-level antibiotic-associated adverse events (e.g., acute kidney injuries, *C. difficile* infections, others).
	Time, resources, support	Data will be collected through a centralized, automated detection and reporting system with manual adjudication performed at the primary study site. Because local resources and IT support are not required, time, resources, and support required to use the centralized system are low for the participating sites and champions.
	Local opinion leaders, Policy Makers	Infectious diseases champions are drivers of practice change and local protocol changes. To leverage the importance of these knowledge leaders, we have the support of policy-making organizations. In addition, process and outcome reports will be provided to local champions to facilitate practice improvements.
Context	Culture	Electrophysiologists commonly conform to local culture about prevention strategies and express concerns about being an “outlier.” Benchmarking is included to demonstrate that the provider is not “an outlier.”
	Evaluation and feedback	Audit and feedback reports will be used to demonstrate to providers that a transition to guideline-concordant recommendations is not harmful to patients, and in fact, improves care.

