#### Cardiac adverse events

Ninety-day incidence of cardiac device infections will be measured using the semi-automated measurement tool adapted for near-real time surveillance. Effectiveness of the tool based on champion feedback will be included in trial results.

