#### Clinical outcomes are secondary in this hybrid type III trial

Clinical outcomes reported are selected to assess the impact of improving adoption of guideline-concordant antimicrobial prophylaxis on important clinical outcomes theoretically linked to appropriate application of peri-operative prophylaxis, specifically, CIED infections (impacted by appropriate pre-procedural antimicrobial use), and AKI and *C. difficile infections* (both impacted by appropriate early discontinuation of antimicrobial use). These data will be extracted from the VA EHR using the automated algorithm and CIED infections will be validated by manual review at the main study site. Similar to the analysis of the implementation outcomes, incidence of key clinical outcomes will be measured pre- and post-implementation at each of the three sites, applying a generalized linear mixed model with allowance for a facility random effect. We will again explore the influence of calendar time in the stepped-wedge design using models described by Nickless et al. [35].

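### The AKI window ends 7 days after the last antimicrobial dose, so shortening courses shortens follow-up and lowers counted AKI even with no true effect

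*Protocol article*

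**What the plan says.** In the protocol article, the section on laboratory-defined AKI and C. difficile gives two windows of the same form. For AKI: "AKI is defined as occurring from the initial date of antimicrobial exposure to within 7 days of the last dose of antimicrobial prophylaxis". For C. difficile: "a positive stool test from the initial date of antimicrobial exposure to within 90 days following the last day of antimicrobial prophylaxis". Both open at first exposure and close a fixed time after antimicrobials stop.

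The primary outcome is the change in the proportion of cases with "guideline-concordant antimicrobial discontinuation within 24 h after skin closure", so the intervention acts directly on when antimicrobials stop. The power section illustrates the target with discordant use that "changed from 50 out of 100 procedures to 35 out of 100 at each site".

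The section on clinical outcomes as secondary outcomes says that "incidence of key clinical outcomes will be measured pre- and post-implementation at each of the three sites, applying a generalized linear mixed model", with a facility random effect and an exploration of calendar time. It mentions no allowance for windows of unequal length.

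Device infection is treated differently: "Ninety-day incidence of cardiac device infections will be measured", with no tie to the last dose. Table 1, listing what the audit tool extracts, speaks of "7-day incidence of acute kidney injury" and gives no start or end point.

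**The concern.** A comparison of incidence before and after an intervention needs each procedure to have the same opportunity to produce an event. Here that opportunity depends on a quantity the intervention changes. A patient with a long course has more days on which an AKI can count than a patient whose course stops within 24 hours. Long courses are, by intention, more common before implementation than after. Counted AKI would then fall for a purely arithmetical reason.

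Adjusting for site or calendar time does not remove this, because the artefact appears when practice changes at each site. The limitations section acknowledges that a non-randomised design weakens causal attribution, but this is a separate problem.

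AKI is one of the two outcomes chosen to show the clinical benefit of early discontinuation. The feedback reports are also meant to reassure clinicians that non-cardiac harms are falling. An apparent fall that is partly built in would weaken the trial's evidence on harm and, if the reports use the same definition, the feedback as well.

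**Working it through.** The article states no AKI or C. difficile rate, power or sample size, so there is no figure of its own to reproduce. The artefact can be computed directly.

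**Inputs from the article:** AKI tail 7 days; C. difficile tail 90 days; discordant use moving from 50% to 35%.

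**Assumptions, not in the article:** a concordant course lasts 1 day; a discordant course lasts D = 3, 5, 7 or 10 days; the background hazard does not depend on antimicrobials, so there is no true effect.

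**Constant hazard.** Window = course length + tail, and expected events are proportional to the window. With a the concordant and b the discordant window, the apparent ratio is

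(0.65a + 0.35b) / (0.50a + 0.50b).

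For AKI, a = 1 + 7 = 8 days:

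| D | b = D + 7 | pre mean | post mean | ratio | apparent fall |
|---|---|---|---|---|---|
| 3 | 10 | 9.0 | 8.70 | 0.967 | 3.3% |
| 5 | 12 | 10.0 | 9.40 | 0.940 | 6.0% |
| 7 | 14 | 11.0 | 10.10 | 0.918 | 8.2% |
| 10 | 17 | 12.5 | 11.15 | 0.892 | 10.8% |

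For C. difficile, a = 1 + 90 = 91 days:

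| D | b = D + 90 | pre mean | post mean | ratio | apparent fall |
|---|---|---|---|---|---|
| 3 | 93 | 92.0 | 91.70 | 0.997 | 0.3% |
| 5 | 95 | 93.0 | 92.40 | 0.994 | 0.6% |
| 7 | 97 | 94.0 | 93.10 | 0.990 | 1.0% |
| 10 | 100 | 95.5 | 94.15 | 0.986 | 1.4% |

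Using risks instead of window lengths (assumed 8-day AKI risk of 2, 5 or 10%) barely changes the AKI ratios. They run from 0.967–0.969 at D = 3 to 0.893–0.900 at D = 10.

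**AKI risk concentrated early.** Let the hazard decay with half-life H, so that the share of events counted by day t is F(t) = 1 − 2^(−t/H). Replace a by F(8) and b by F(D + 7):

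| H (days) | D = 5 | D = 7 |
|---|---|---|
| 2 | 0.993 | 0.992 |
| 3 | 0.984 | 0.980 |
| 5 | 0.972 | 0.963 |

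The apparent fall is then about 1 to 4%. For example, with H = 5 and D = 7, F(8) = 0.670 and F(14) = 0.856, so the ratio is 0.735/0.763 = 0.963.

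**With a fixed window,** a = b, and the ratio is 1.00 for both outcomes under every hazard shape above.

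**The case against.** The case for leaving the definition alone has several parts.

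- **Secondary outcome, modest size.** AKI is secondary and the study is powered for adoption. For scale, the article gives only 50% power to detect a halving of device infections. This stands, and it limits severity.
- **The size depends on assumptions.** Course lengths and hazard shape are not in the article, and early-concentrated risk brings the fall down to 1 to 4%. This stands for the size. The direction was the same in every scenario computed.
- **A time-at-risk offset could sit in the analysis plan.** An article may leave that out, and its absence is not the point here. An offset corrects exactly only under constant hazard. With H = 3 and D = 5, counts fall to 0.984 while time at risk falls to 0.940, so the rate ratio is 0.984/0.940 = 1.047, a spurious rise.
- **An exposure-based window targets drug harms.** That is a sound reason for describing events around exposure, and for keeping the definition as a sensitivity analysis. It does not suit a comparison of periods whose exposure length differs by design.

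A reader might also infer more than the article supports:

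- That C. difficile is affected like AKI. The 90-day tail dominates the window, so it is not.
- That Table 1 contradicts the definition. It gives no anchor, so this is an ambiguity; for the same reason it is not shown that the reports carry the bias.
- That the artefact is far larger. If discordance fell from 50% to zero, the constant-hazard AKI fall would be 11% (8/9.0 = 0.889) to 36% (8/12.5 = 0.640). But the shift the article uses is 50% to 35%.

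**Conclusion.** The point holds for AKI. Following the stated definition biases the pre/post AKI comparison in the intervention's favour. At the article's own 15-point shift the spurious fall is about 3 to 11% under constant hazard with assumed 1-day concordant and 3 to 10 day discordant courses. It is about 1 to 4% if AKI risk is concentrated early, with a half-life of 2 to 5 days and 5 to 7 day courses. For C. difficile it is about 0.3 to 1.4% and can be ignored in practice. The primary outcome does not use these windows and is unaffected. Severity is moderate: a real and avoidable bias of modest size in a secondary outcome, not one that undermines the trial.

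**What to change.** - For the comparative analysis, count AKI over one fixed window from the procedure date (or first dose), identical for every procedure and long enough to cover the usual longest course plus 7 days. With a 10-day course, course plus tail is 17 days, so 0 to 21 days would serve and 0 to 14 would not. Anchoring at the procedure date also gives a window to any procedure without antimicrobials, which the present definition lacks.
- Count C. difficile over a fixed window in the same way, for consistency.
- Keep the last-dose definition as a sensitivity analysis.
- State the anchor in Table 1 and use the same fixed window in the feedback reports.

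The work is a change of definition in the extraction code. There are two statistical costs. A longer window picks up background events in both periods, which slightly dilutes a true relative effect. Events after unusually long courses may also fall outside it; the sensitivity analysis covers those.
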